### Randomization and blinding

Intra-operatively, the treating surgeon judges whether the patient is eligible for definite inclusion. Prior to formation of the temporary loop ileostomy, loop or split colostomy, included patients will be randomized. Patients will be randomized in a 1:1 fashion to the C-Qur™ Film arm (treatment arm) or the control arm. The randomization will be stratified by operative technique (open or hand-assisted laparoscopy). The allocation sequence will be computer-generated through the web-based program Alea©. A researcher who does not participate in the data analysis will manage the randomization process. This way, the researcher who will perform the data analysis is blinded from treatment allocation. Concealment of treatment allocation and blinding of the surgeon performing the index procedure is not possible because the patient will either get the intervention or does not get an intervention at all. Randomization will be noted in the operation reports, allocation will not.

The patient and doctor at the surgical ward who will complete the case report form during the post-operative period is blinded from treatment allocation. To achieve blinding during the data collection of outcome parameters, the surgeon who will perform the ostomy takedown procedure, will not be the same surgeon as the one who performed the index procedure. Because of the absence of clinical notes regarding allocation, however, the initial surgeon is allowed to do the ostomy takedown in case of man-power or organizational problems.

During the postoperative period after the ostomy takedown, the physician at the ward, who will collect the data regarding the post-operative parameters, will be blinded from the treatment allocation of the patient. The patient will stay blinded for the received treatment.

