### Design

The CLIPEUS trial is a prospective, investigator-initiated, randomized controlled, double-blinded, multicenter trial. Treatment with the C-Qur™ film adhesion barrier will be compared with no treatment with an adhesion barrier in patients undergoing colorectal surgery with temporary diverting ostomy. The surgeons who have agreed to participate in the study and perform the index procedures will be trained in the placement of C-Qur™ Film and in adhesion mapping.

Patients will be included at the outpatient clinics of the participating centers (Radboud University Medical Center, Nijmegen; Catharina Hospital, Eindhoven; Atrium Medical Center, Heerlen; Maxima Medical Center, Veldhoven; Gelderse Vallei Hospital, Ede) by the treating surgeons. During the operation, when the definite decision to create a temporary ostomy is made, patients are randomized 1:1 to either the treatment arm (C-Qur™ film) or the control arm (standard treatment: no adhesion barrier, no placebo). In patients assigned to the treatment arm, the C-Qur™ Film must be applied beneath the incision. The C-Qur™ film can also be applied to other areas considered to be adhesiogenic (for example, the dissection site and ostomy site, but not around the anastomosis). The number of C-Qur™ Film sheets placed is limited to a maximum area of coverage of 774 cm^2^ (Table 1). Patients will return 8 to 16 weeks post-colorectal resection to have their diverting ostomy taken down. During the takedown, the incidence, extent and severity of the adhesions will be evaluated.

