Patients will return 8 to 16 weeks after index surgery to have their ostomy taken down. Clinical follow-up to obtain update(s) on adverse events (AE’s), adhesion-related events, changes in concomitant medications, the presence/absence of surgical site infection (SSI) and the type of SSI (if applicable) will be done during the admission for ileostomy/colostomy takedown. Weight and vital signs will be noted and the following laboratory investigations will be repeated: CRP, sodium (Na), potassium (K), urea, creatinine, hemoglobin, white blood cell count, platelet count, international normalized ratio (INR) and prothrombin time (PT).

Patients in both groups will undergo the same procedure for ostomy closure. To evaluate the adhesions at the loop ileostomy/colostomy site, the incidence, severity and extent of adhesions around the ostomy have to be evaluated during takedown. The time required for takedown of the ostomy is defined as the time from start of the takedown to the time the bowel is repositioned in the abdomen, and this time will be noted on the CRF. The severity of adhesions will be scored according to the Zühlke classification (see Table 2). To assess the extent of adhesions, the ostomy is divided in four quadrants (Figure 2). The extent of adhesions is scored as the number of quadrants containing adhesions (Table 3). After the ileostomy/colostomy takedown is completed, the surgeon will introduce a laparoscope at the ostomy site and evaluate the incidence, extent and severity of adhesions at the incision site and at other areas potentially injured (and covered) during the initial procedure. The severity will be scored according to the Zühlke classification (see Table 2). The extent of adhesions underneath the incision site will be scored through estimation of the area covered by adhesions as a percentage of the total area underneath the incision. The incidence and severity of adhesions at other areas potentially injured during the initial procedure will be scored according to the Zühlke classification (see Table 2).

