### Statistics

In general, for continuous variables, the mean, standard deviation, median, IQR, minimum and maximum values will be presented. Groups will be compared using the *t*-test or Mann-Whitney *U* test, as appropriate, based on the distribution of the data. For categorical variables, the frequencies and percentage within each category will be calculated. Groups will be compared using the chi-square or Fisher’s Exact test, as appropriate, based on the expected counts. All available data will be summarized. Demographics, preoperative, perioperative, and postoperative parameters will be reported and compared for both groups. Descriptive statistics will be presented to describe the trial results. Missing data will be evaluated by the investigators, and appropriate action will be undertaken*.* In case of skewed baseline data between groups, results will be corrected for this data.

Our primary analysis will focus on the effectiveness and safety of the C-Qur film between the treatment group and the control group. A chi-square or Fisher’s Exact test will be performed to assess a significant improvement in the incidence, on the Zühlke score of adhesions underneath the incision site, underneath the loop ileostomy or loop/split colostomy site, and for the extent of adhesions underneath the loop ileostomy or loop/split colostomy site as well. The extent of adhesions underneath the incision site and the time needed for takedown of the ileostomy or loop/split colostomy will be compared using a *t*-test. To assess the safety of the C-Qur film the total incidence of postoperative complications will be compared using a *t*-test or a Mann-Whitney *U* test. The mortality and the incidence for each separate complication will be compared using a chi-square or Fisher’s Exact test.

Subgroup analysis will be performed on laparoscopic versus open colorectal resection, and on ileostomy versus colostomy for the incidence, extent and severity of adhesions as described above. Since data collection of the outcome parameters is not blinded when the same surgeon who performed the index procedure also takes down the ostomy, subgroup analysis will be performed for patients with and without blinded data collection of outcome parameters.

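### The index surgeon, who knows the allocation, may score the primary outcome; the reason given does not blind that surgeon, so the double-blinded label is not secured for that outcome

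*Protocol article*

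**What the plan says.** The Abstract and the Design section call the trial double-blinded; Design has "randomized controlled, double-blinded, multicenter trial".

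Randomization and blinding makes three statements about the surgeon:

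- For the index operation, "blinding of the surgeon performing the index procedure is not possible".
- To keep outcome collection blind, the takedown surgeon "will not be the same surgeon as the one who performed the index procedure".
- As an exception, "the initial surgeon is allowed to do the ostomy takedown in case of man-power or organizational problems". The reason opens with "Because of the absence of clinical notes regarding allocation".

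Data recording and follow-up has the surgeon at takedown pass a laparoscope through the ostomy site and assess adhesions at the incision. Outcome measures makes their incidence the primary outcome.

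Statistics says that "data collection of the outcome parameters is not blinded when the same surgeon who performed the index procedure also takes down the ostomy" and plans a subgroup analysis by whether scoring was blinded.

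On secondary sites, Data recording and follow-up has the surgeon assess adhesions "at other areas potentially injured (and covered) during the initial procedure". Outcome measures defines the same outcome by potential injury alone. The Control arm section gives controls neither film nor placebo.

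**The concern.** The reason for the exception does not support it. Keeping allocation out of the operation report can blind a second surgeon. It cannot blind the one who applied the film or closed without it.

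This reaches the primary outcome. Whether an adhesion is present is a yes/no visual judgement, and the lowest positive grade in Table 2 is a filmy adhesion that separates easily. A scorer who knows that film was placed could lean towards recording none, and error in that direction favours the film. The exception has no cap, and nothing removes these scores from the main comparison.

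The parenthesis about covered areas is a smaller matter. Only film patients can have a covered area, so a literal reading would give the arms different sets of sites, or would tell the scorer where film lay.

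**Working it through.** **1. The passages side by side.**

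| Section | Same-surgeon takedown |
|---|---|
| Randomization and blinding | Allowed, because allocation is not in the notes |
| Data recording and follow-up | The takedown surgeon scores the incision site |
| Statistics | Scoring is then not blinded |
| Abstract; Design | Trial is double-blinded, without qualification |

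The first row relies on the notes to protect blinding, and the third says blinding is lost. The third is right on the protocol's own facts, since the index surgeon cannot be blinded.

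**2. The plan's own figure.** Inputs from Analysis and sample size: 94% v 64%, two-sided alpha 0.05, 80% power, 32 evaluable per group. Full enumeration of Fisher's exact test at 32 per group gives power 80.9%, so the plan's figure reproduces. The sample size is not in question.

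**3. How large could the bias be?** Taken from the protocol: a rate of 94%, 32 per arm, and chi-square or Fisher's test chosen by expected counts. Assumed, because the protocol gives no figure:

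- the film is inert, so the true rate is 94% in both arms;
- a share f of takedowns is done by the index surgeon;
- that surgeon records as absent a share m of true adhesions in film patients only;
- Fisher's test is used when an expected count is below 5.

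Apparent film rate = 0.94 × (1 − f × m).

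- f = 0.1, m = 0.2: 0.94 × 0.98 = 0.921, a spurious difference of 1.9 points.
- f = 0.3, m = 0.2: 0.94 × 0.94 = 0.884, or 5.6 points.
- f = 0.5, m = 0.3: 0.94 × 0.85 = 0.799, or 14.1 points.

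The rejection probability is the sum, over all pairs (a, b) that the test calls significant, of Bin(a; 32, 0.94) × Bin(b; 32, apparent film rate):

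| f | m | Plan's test rule | Fisher only |
|---|---|---|---|
| 0 | – | 0.4% | 0.3% |
| 0.1 | 0.2 | 0.8% | 0.7% |
| 0.2 | 0.2 | 1.8% | 1.6% |
| 0.3 | 0.2 | 3.8% | 3.3% |
| 0.5 | 0.3 | 28% | 23.5% |

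The baseline is far below 5% because exact testing is conservative at rates near 94%. Uncorrected chi-square throughout would give 4.0% without bias and 41.4% in the last row.

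**4. Can the planned subgroup settle it?** Power of Fisher's test at 94% v 64% among blinded scores alone is 68% with 24 per arm, 42% with 16 and 8% with 8. With few exceptions the blinded-only result stays informative; with many it does not.

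**5. Covered areas.** Outcome measures and the closing sentence of the takedown description in Data recording and follow-up both refer to potentially injured areas without mentioning cover. The parenthesis appears once, and the incision site exists in both arms.

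**The case against.** The protocol is open about the problem. A different surgeon is the rule, the exception is tied to staffing or organization, and Statistics admits the loss of blinding and plans an analysis by it. Randomization and blinding also says who is blinded: patient, ward doctor and analyst. All of this stands, and nothing is concealed. It does not rescue the stated reason, and it leaves unblinded scores in the primary comparison under an unqualified label.

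The magnitude rests on assumed shares. An f of one half sits poorly with a rule written as an exception, and m assumes error in one direction only. This also stands. A reader might infer that the false-positive rate is in fact 28%, or is certainly inflated. The documents do not support that: under the plan's test rule, only the harshest case shown exceeds 5%.

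Two further inferences go too far. One is that scorers are obliged to assess covered areas. That rests on a single parenthesis about a secondary outcome, and the outcome definition does not repeat it. The other is that the injured areas are named by a surgeon who already knows the allocation. No section says who lists them or when, and serosal injuries and enterotomies are recorded for all patients.

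Finally, requiring a second trained scorer or an image reader would add a resource exactly when staff are short. Design describes training in adhesion mapping only for surgeons who perform the index procedures. That objection is accepted.

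**Conclusion.** The point holds in this form. The absence of notes does not blind the index surgeon, Randomization and blinding conflicts with Statistics, and double-blinding is not secured for the primary outcome wherever the exception is used. The amount of bias cannot be stated, because the protocol gives no share of same-surgeon takedowns and no misclassification rate. Under the assumptions in the working, the spurious difference runs from about 2 to 14 points, against a planned difference of 94 − 64 = 30. The chance of a false significant result runs from 0.8% to 28%, against 0.4% without bias. The wording on covered areas is a separate inconsistency, confined to a secondary outcome.

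**What to change.** The Trial status section says inclusion has not started, so all of this can be changed in time.

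1. Delete the justification based on the absence of notes, and bring Randomization and blinding into line with Statistics.
2. Add a CRF field recording whether the scorer did the index operation.
3. Name the blinded-only comparison, already half of the planned subgroup split, as a sensitivity analysis reported beside the primary result.
4. Describe the trial as patient-, ward- and analyst-blinded, with assessor blinding where achieved.
5. In every patient, list the injured or adhesiogenic areas on the CRF before allocation is opened. Score that list in both arms and delete the parenthesis about cover.

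Where a team member who was not at the index operation is already present, that person may enter the incision-site score; no extra assessor is required. The cost is two CRF fields and a less favourable blinding label. The sample size does not change.

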### Unblinding protocol

A Data Safety Monitoring Board (DSMB) meeting for safety assessment will be scheduled once every 15 patients have been enrolled. The study will be deblinded when there is a higher mortality rate or incidence of surgical complications than can be expected from data found in the literature. The deblinding will be performed by the same researcher who performs the randomization procedure.

Patients will be informed on request about the performed procedure only after completing the quality-of-life questionnaires 1 year postoperatively.

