### Ethics and informed consent

This study is conducted in concordance with the principles of the Declaration of Helsinki [17] and Good Clinical Practice guidelines. The protocol was ethically approved by the official Independent Review Board Nijmegen (2013/470) and registered nationally (NL45940.091.13) [15]. A Data and Safety Monitoring Board (DSMB) is established to perform safety surveillance and to perform interim analysis on the safety data, as described.

Patients will be screened in the outpatient clinic for participation in this study by a surgeon in one of the hospitals that will contribute to this study. Each patient must meet the inclusion/exclusion criteria of this trial. All potentially eligible patients are required to sign an informed consent after careful consideration. Patients have to sign the informed consent prior to the index procedure.

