### Analysis and sample size

It is hypothesized that the use of the C-Qur™ Film underneath the primary incision reduces the incidence of adhesion at the incision by 30%. This hypothesis is based on the supporting documentation for Seprafilm™ (treatment) versus Control (no treatment) with an adhesion rate of 94% in the control group and 64% in the treatment group [18–22]. We estimate a total drop out of 25% in this study, comprising 10% regular drop out and 15% drop out because of anastomotic leakage. A 15% drop out because of anastomotic leakages is chosen because it is the upper limit of the incidence of this complication. Assuming that the C-Qur™ Film group performs similarly to Seprafilm™, a total of 84 patients, (32 + 10 per group (25% drop out)) would be needed in a randomized study, with 80% power and two-sided alpha = 0.05 in order to detect a 30% reduction in incidence of adhesions.

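### The deblinding trigger compares event rates with the literature and not film with control, so it responds to the overall event level and cannot identify a film effect

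*Protocol article*

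**What the plan says.** The Unblinding protocol section of the protocol article sets a DSMB safety meeting that "will be scheduled once every 15 patients have been enrolled". The study is to be "deblinded when there is a higher mortality rate or incidence of surgical complications than can be expected from data found in the literature", and the researcher who runs the randomisation carries out the deblinding. Ethics and informed consent gives the DSMB the task "to perform safety surveillance and to perform interim analysis on the safety data, as described", which points back to that rule.

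The trigger names an external comparator. It states no reference rate, no margin for chance, no arm to which the rate applies, and no contrast between arms. The Statistics section does compare film with control on mortality and on each complication, but not as the deblinding trigger.

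The only complication rate the article gives for its own population is in Analysis and sample size: "A 15% drop out because of anastomotic leakages is chosen because it is the upper limit of the incidence of this complication".

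**The concern.** The trial randomises 1:1, so a concurrent control is available at every look. Whether the film causes harm is a question about film against control. A literature rate answers a different one: whether these hospitals and patients have more events than published series. Case mix, complication definitions and intensity of recording all move that answer without any film effect.

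The article's own Background shows why this matters. The leak signal for the comparator film came from a randomised study with a concurrent control group, and this protocol bars film from the anastomosis.

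Two things are at stake. A film-related excess may go unflagged if the overall rate stays below the literature figure. Or allocation may be opened for reasons unrelated to the film, in a trial whose primary outcome is a surgeon's laparoscopic judgement. The Statistics section already treats unblinded assessment as serious enough for a subgroup analysis.

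**Working it through.** **Inputs from the article.** Allocation is 1:1 and the total is 84, that is 2 × (32 + 10). The 32 per group reproduces: for 94% against 64% at two-sided 0.05, Fisher's exact test has 79.0% power at 31 per group and 80.9% at 32. Looks every 15 patients fall at 15, 30, 45, 60 and 75, since 84/15 = 5.6. The rule itself has no stated operating figure to reproduce.

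**Assumptions.** No reference rate is given, so references of 1% to 40% were tried. The 15% leakage figure is used only as an illustration; the article offers it as a dropout allowance. The rate is pooled over arms, because it is judged before deblinding. Every enrolled patient is counted at each look.

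**Rule as worded, without margin.** With cumulative events X at look n and reference r, it fires if X > r × n. For r = 15% the products are 2.25, 4.5, 6.75, 9 and 11.25, so it fires at 3, 5, 7, 10 or 12 events. P(fires at some look) = 1 − P(X ≤ r × n at all five looks).

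**Same overall level, opposite truth (r = 15%).** The pooled rate is 10% in both arms in the first case, and (5% + 15%)/2 = 10% in the second. At 75 patients each case expects 7.5 events against the 12 needed.

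| Control | Film | Fires at some look |
|---|---|---|
| 10% | 10% | 31% |
| 5% | 15% | 29% |

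The second figure is 29% or 31% depending on which arm has the odd patient among the first 15. At the 75-patient look alone it is 6-7%. The rule sees only the pooled level and cannot separate the two cases.

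**Reference equal to the true rate, no film effect.** First look at 2%: 1 − 0.98^15 = 26%. First look at 15%: P(X ≥ 3 of 15) = 40%. Over five looks:

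| Reference = true rate | Fires at some look |
|---|---|
| 1% | 53% |
| 2% | 64% |
| 3% | 70% |
| 5% | 73% |
| 10% | 69% |
| 15% | 70% |
| 20% | 65% |
| 30% | 72% |
| 40% | 68% |

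Mortality and surgical complications taken together as two independent triggers give 83-93%. Independence is an assumption, and the two are plausibly correlated.

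**True rate below a 15% reference, no film effect.** Firing is 47% at a true 12%, 31% at 10% and 17% at 8%.

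**With a margin.** An exact one-sided 5% binomial bound at each look lowers chance firing over five looks to about 6-11%. Detection of 5% against 15% with a 15% reference then drops to about 0.4%.

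**Baseline and reference held fixed, no margin.**

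| Reference | Control | Fires, film = control | Fires, film = 3 × control |
|---|---|---|---|
| 15% | 5% | 4.5% | 29% |
| 15% | 10% | 31% | 93% |
| 15% | 15% | 70% | about 100% |
| 5% | 5% | 73% | 98% |

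A three-fold excess is missed in 100% − 29% = 71% of trials in the first row, where chance firing is only 4.5%. In the last two rows chance firing is high and the excess is nearly always caught.

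**Film arm alone.** If the rate were read in film patients only, chance firing is 31-77% per trigger over the same references. A 15% film rate against a 15% reference fires in 65% of trials whatever the control rate, because control does not enter.

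**The case against.** The wording refers to what can be expected, and a DSMB may well allow for chance when it judges that. With such a margin, chance firing is about 6-11%. A reader might infer that the trigger will usually fire by chance. The article does not support that: it requires no margin but rules none out, it gives no reference rates, and the high figures need the true rate to lie close to the reference.

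A reader might also infer that the rule fires more often without harm than with a three-fold excess. That compares different baselines. With control rate and reference fixed, harm raises firing in every row above. Nor does one reference produce both failures at full size, so it would be too strong to say that the rule neither protects patients nor preserves blinding.

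It is also fair that deblinding is assigned to the randomisation researcher, that patients learn their allocation only after the one-year questionnaires, and that the article does not say surgeons or ward doctors would be told. Numerical references and margins may sit in a fuller protocol or DSMB charter. A between-arm significance test would be weak: at 42 per arm, Fisher's test has about 20% power for 5% against 15%.

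These points limit the size of the concern. They do not remove it. The comparator is stated, not left open, and it is the literature. Adding a margin controls chance firing but makes an external comparison still less able to find a film effect. The low power argues for DSMB judgement on the difference with its interval, not for setting the control arm aside.

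**Conclusion.** The concern holds as a badly chosen comparator. The stated trigger tracks the overall event level: against an illustrative 15% reference it fires in about 31% of trials with 10% leakage in both arms, and in about 29% with 15% against 5%. Chance firing of about 53-73% per event type applies only if the reference is near the true rate and no margin is used. Missing about 71% of three-fold excesses applies only if the reference lies well above the control rate.

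All of these figures rest on assumed reference rates and five looks. Apart from the film-arm figures, they also rest on pooled counting. The conclusion that the rule carries no film-control information does not depend on them.

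This should be corrected before inclusion starts. It does not invalidate the design: firing leads to deblinding, not expressly to termination, and the final analysis does compare the arms.

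**What to change.** Replace the trigger sentence in Unblinding protocol, or state the following in the DSMB charter and refer to it:

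- At each 15-patient look, the independent randomisation researcher gives the DSMB closed-session tables by arm for mortality, anastomotic leakage and surgical complications.
- The DSMB judges the film-control difference with its confidence interval. Literature rates serve as background only. No significance threshold is set as the trigger.
- Any deblinding is confined to the DSMB. Takedown surgeons, ward doctors, patients and the analyst stay blinded unless the DSMB recommends otherwise.

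The cost is about one paragraph. The researcher's role already exists, and Trial status says inclusion has not begun. The downside is small: DSMB members see arm-level data. Intervals will be wide at these numbers, so the DSMB still has to use judgement.
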